##### Quality of life

We use the short version of the World Health Organization’s quality of life questionnaire (WHOQOL-BREF) for the dimensional assessment of quality of life (Bruesch et al., 2011). It is a 26-item self-report questionnaire measuring the subjective perception of the individual’s own life. The questionnaire concerns different fields: physical health (including among others pain, fatigue or working abilities), psychological health (including among other positive and negative emotions and self-esteem), social relations (including among other private life or the available social support) and living environment (including among other financial resources, access to information resources, recreation). Two introducing items are related to the overall quality of life. One score of specific quality of life is available for each domain and a general quality of life score is available by combining the specific scores. This instrument has previously been translated and validated in French (Leplège et al., 2000).

##### Other measures

###### Sociodemographic information

Including gender, age, marital status, familial situation at home (alone, spouse, child, etc), academic level, and socioeconomic status are collected or during the first interview either from the medical records.

###### Medical condition and treatment

Data about the medical condition of the participants including previous and present affections (somatic, neurologic, psychiatric), family history neurological affections, medical treatment at hospital entrance, vascular risk factors (BMI, diabetes, cholesterol, high blood pressure, alcohol and other substance use).

###### Stroke characteristics and functional deficit

Stroke localization (right or left hemisphere) and type (ischemic or hemorrhagic) based on medical imageries and exams conclusions. In case of ischemic stroke, we record if patients have received a thrombolytic treatment. Functional deficit is assessed with the National Institutes of Health Stroke Scale (NIHSS). This scale is administered by a trained health professional (physicians, nurses) and is composed of 15 items measuring neurological motor and cognitive deficits after a stroke. Items are related to consciousness, cognition, inattention, speech, sensory and motor functioning, visual fields functioning and ataxia (Meyer and Lyden, 2009; Zandieh et al., 2012).

#### Data Analysis

##### Outcomes and statistical methods for primary objectives

Feasibility and acceptability of the EMA method will be assessed by examination of acceptance and compliance rate, fatigue effects and reactivity to assessment: completion rate during each week, participation at follow-up weeks (phases 2 and 3), missing data and assessment duration across time during each phase. Descriptive analysis will be performed to describe feasibility and acceptability. Compliance will be assessed as the completion rate of EMA questionnaires. This rate will be calculated as the ratio of completed questionnaires to all sent questionnaires within each phase (four questionnaires per day during 7 days for each participant). Follow-up participation will be the ratio of number of participants at phase 2 and 3 to the number of participants at inclusion (phase 1). Fatigue effect will be calculated as the evolution of the within-day mean of missing data. Reactivity to EMA assessment will be estimated by comparing anxiety, depression and quality of life scores (self-reported questionnaires and clinicians’ ratings) of EMA participants to other participants (not involved in the EMA part of the study, more information is given in the limitations section below).

Validity of the method will be examined by using three different EMA indexes consisting in different aggregation of anxious and depressive symptoms assessed with EMA for each participant: a global anxiety and depression index (including all 11 symptoms assessed), a specific depression index (including sadness, anhedonia, fatigue, concentration difficulties, negative thoughts, pessimism) and a specific anxiety index (including anxiety, agitation, physical tension, irritability, concentration difficulties).

Validity will be assessed by using Pearson correlations between EMA indexes with self-reported questionnaires’ scores and clinicians’ ratings. Only participants with a satisfying minimum within- and between-day compliance will be included in this analysis (i.e., at least 5 EMA questionnaires filled). We will observe associations between: the global EMA index and the overall score of the HADS; the depression EMA index with the BDI score, the HADS depression subscale score and the MADRS score; the anxiety EMA index with the HADS anxiety subscale score and the HAM-A.

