## Abstract

**Context:** Stroke has several consequences on survivors’ daily life even for those who experience short-lasting neurological symptoms with no functional disability. Depression and anxiety are common psychological disorders occurring after a stroke. They affect long-term outcomes and quality of life but they are difficult to diagnose because of the neurobiological consequences of brain lesions. Current research priority is given to the improvement of the detection and prevention of those post-stroke psychological disorders. Although previous studies have brought promising perspectives, their designs based on retrospective tools involve some limits regarding their ecological validity. Ecological Momentary Assessment (EMA) is an alternative to conventional instruments that could be a key in research for understanding processes that underlined post-stroke depression and anxiety onset. We aim to evaluate the feasibility and validity of anxiety, depression and coping EMA for minor stroke patients.

**Methods:** Patients hospitalized in an Intensive Neuro-vascular Care Unit between April 2016 and January 2017 for a minor stroke is involved in a study based on an EMA methodology. We use a smartphone application in order to assess anxiety and depression symptoms and coping strategies four times a day during 1 week at three different times after stroke (hospital discharge, 2 and 4 months). Participants’ self-reports and clinician-rates of anxiety, depression and coping are collected simultaneously using conventional and standard instruments. Feasibility of the EMA method will be assessed considering the participation and compliance rate. Validity will be the assessed by comparing EMA and conventional self-report and clinician-rated measures.

**Discussion:** We expect this study to contribute to the development of EMA using smartphone in minor stroke population. EMA method offers promising research perspective in the assessment and understanding of post-stroke psychological disorders. The development of EMA in stroke population could lead to clinical implications such as remotely psychological follow-ups during early supported discharge.

**Trial registration:** European Clinical Trials Database Number 2014-A01937-40

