### Objectives

This article aims to describe an innovative study design for the assessment and investigation during 4 months (following stroke), of minor stroke patients’ psychological health (depression, anxiety), coping strategies and quality of life combining classical standard scales and questionnaires with EMA using a smartphone application.

Primary objective is a methodological one. We aim to evaluate feasibility, acceptability, quality and reliability of data collected by EMA in minor stroke patients at different times and in different contexts during the first 4 months following a stroke.

Secondary objectives focus on studying psychopathological manifestations after stroke and the processes involved in their onset and evolution. Thus, we have several objectives considering these points: (1) to estimate the frequency and assess the evolution of anxiety and depression in minor stroke population, (2) to determine the risk factors and determinants of PSA and PSD in minor stroke patients and to study if coping is a reliable predictor, (3) to describe the clinical and psychosocial characteristics of depressed and anxious individuals after a minor stroke, (4) to describe symptomatic characteristics of PSD and PSA, (5) to study the sequences and dynamic processes between anxiety and depression symptoms, coping strategies and contextual and ecological factors at different times (during the first days, at 2 months and at 4 months) and contexts (hospitalization, discharge, return to work) after stroke.

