#### EMA and Ad Scientiam Tool

In this study, the EMA is designed as a smartphone application: Ad Scientiam Research^®^. The app is programmed on participants’ personal (or lent) smartphones.

Each EMA phase (phase 1b = hospital discharge, phase 2 = 2 months post stroke and phase 3 = 4 months post stroke) lasts 1 week. The participants answer four brief electronic interviews (<3 min) per day during 7 days. The app sends prompts to inform the participants that they can answer the interview.

Time of prompts are fixed for each patient and randomized across patients. They occur within each of the following time periods: 7–10 am, 11 am to 2 pm, 3–6 pm and 7–10 pm. Each prompt is spaced out of at least 2 h from the prior and next prompts. A randomly generated daily schedule is submitted to participants. The time of prompts can be adjusted at each phase in order to suit participants’ typical daily schedules (wake, work, and sleep). The application permits responses to be provided within 30 min after each prompt.

The EMA consists in 32 screens related to seventeen questions split into three questionnaires (the exact wording is available in Supplementary File 1): (1) present situation and context; (2) anxiety and depression symptoms; (3) positive and negative events.

The selected items are based on previous EMA studies (Jean et al., 2013) or built specifically for the study on the basis of validated questionnaires. Questions composing questionnaire 2 have been adapted from the MINI (Major Depressive Episode and General Anxiety Disorder modules; Lecrubier et al., 1997; Sheehan et al., 1998). The anxiety and depression symptoms that can possibly variate within a day as it was previously done for an EMA study of depression in stroke population (Sibon et al., 2012) have been selected. For the questionnaire 3, questions about positive and negative events have been adapted from the Inventory of Small Life Events (Zautra et al., 1986) previously used and adapted for EMA (Petit, 2009; Mazure et al., 2014). Questions about the coping strategies for facing the negative event have been adapted from the Brief-COPE (Carver, 1997) and is an original EMA measure of coping created for the present study.

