#### Content of EMA Questionnaires

Questionnaire 1 presents situation and context (multiple choice list): place, company, activity.

Questionnaire 2 – depression and anxiety symptoms (7 points Likert scale): sadness, anhedonia, fatigue, diminished concentration ability, negative thoughts on oneself, pessimism, anxiety, psychomotor agitation, physical tension, irritability.

Questionnaire 3 is related to positive and negative events that happened in the hours before the prompt: category of the most positive event and evaluation of the positive degree of this event on a 7-points Likert scale; category of the most negative event and evaluation of the negative degree of this event on a 7-points Likert scale; description of the reaction when confronted to this negative event. Fourteen sentences are answered by “yes” or “no” if they describe or not the behavior for coping with the situation.

Ecological Momentary Assessment questionnaires are explained and practiced with research staff at home when the first week of EMA begins. Then the procedure is reminded at the beginning of each week of EMA. All participants are contacted after 2 days during each EMA week to resolve any questions or difficulties.

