##### Coping strategies with stroke-related stress

Coping strategies are measured with the Brief-COPE (Coping with Problem Experienced short version) (Carver, 1997). The Brief-COPE is a 28-item self-report questionnaire divided in 14 subscales (two items by subscale) corresponding to conceptually differentiable coping reactions to stress: active coping, planning, instrumental social support, emotional social support, venting, positive reframing, acceptance, denial, self-blame, humor, religion, self-distraction, substance use and behavioral disengagement. We use a French validation of this instrument (Muller and Spitz, 2003). We refer to the dispositional version of the questionnaire and we have rephrased the wording of the instructions to focus on reactions concerning stroke-related stress. Each item is answered on a four-level scale corresponding to the frequency of the reaction when the individual is confronted to stroke-related stress situation.

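### The abstract promises validation of the EMA coping measure, but the listed validity analysis compares only mood indexes and never sets EMA coping against the Brief-COPE

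*Protocol article*

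**What the plan says.** The abstract states the aim as: "We aim to evaluate the feasibility and validity of anxiety, depression and coping EMA for minor stroke patients". It says validity will be judged by "comparing EMA and conventional self-report and clinician-rated measures", and that conventional measures of all three constructs are collected alongside EMA.

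The Objectives section words the primary objective differently: "We aim to evaluate feasibility, acceptability, quality and reliability of data collected by EMA in minor stroke patients". Neither validity nor coping is named there, but reliability is. The Clinical Implications section again says the results will inform reliability, alongside feasibility and validity.

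On the coping instrument, the section on the EMA tool says that the coping questions were adapted from the Brief-COPE and that the result "is an original EMA measure of coping created for the present study". Its form is given under Content of EMA Questionnaires: "Fourteen sentences are answered by “yes” or “no” if they describe or not the behavior for coping with the situation". The conventional instrument has a parallel structure: "The Brief-COPE is a 28-item self-report questionnaire divided in 14 subscales". Table 1 marks both for hospital discharge (phase 1b), 2 months (phase 2) and 4 months (phase 3).

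The section on statistical methods for primary objectives states: "Validity of the method will be examined by using three different EMA indexes consisting in different aggregation of anxious and depressive symptoms". These are a global, a depression and an anxiety index, to be related to named scales by Pearson correlation.

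**The concern.** Under the plan as written, the study would end without any evidence on whether the EMA coping items agree with an established coping questionnaire, although the abstract announces that comparison. The gap falls on the one EMA component that the article itself labels as original. It also carries forward: secondary analysis (5) puts coping assessed by EMA into the multilevel VAR model, so links between coping and symptoms would be interpreted with no support for the coping measure.

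Reliability raises a smaller question of the same kind. It is named in the primary objective and promised in the discussion, but no listed analysis estimates it. It also bears on the study's own benchmark. Correlations above 0.70 are expected, and participants with as few as 5 completed questionnaires enter the analysis. Without a reliability estimate, a lower correlation could reflect noisy indexes as easily as poor validity.

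**Working it through.** The point rests on matching stated aims to listed analyses; arithmetic plays a minor part.

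**1. Validity pairings in the primary analysis**

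| EMA index | Comparators | Pairs |
|---|---|---|
| Global | HADS total | 1 |
| Depression | BDI, HADS depression, MADRS | 3 |
| Anxiety | HADS anxiety, HAM-A | 2 |
| Coping | none | 0 |

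The total is 1 + 3 + 2 = 6 pairs, of which 0 concern coping. No EMA coping score is defined.

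**2. Whether the secondary analyses fill the gap**

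- (1) and (3) concern the frequency of depression and anxiety and the description of affected participants.
- (2) uses coping strategies as a predictor and does not say which instrument supplies them.
- (4) relates EMA to self-report and clinician ratings, for depression and anxiety symptoms only.
- (5) uses coping assessed with EMA as a variable in the VAR model.

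None compares EMA coping with the Brief-COPE.

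**3. Whether the comparison is possible with the planned data**

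There are 14 EMA coping sentences and 14 Brief-COPE subscales, both collected at phases 1b, 2 and 3. If each sentence maps to one subscale, this gives 14 matched pairs per phase and 14 × 3 = 42 over the study. The mapping is an assumption: the item wording is in a supplementary file that is not shown.

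**4. Reliability**

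The primary analyses listed are acceptance, compliance, follow-up participation, missing data, assessment duration, fatigue, reactivity and the validity correlations. Missing data and compliance speak to data quality. None of the items estimates measurement error or the consistency of an index.

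**5. Precision to expect**

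The plan's own figure reproduces: 40 × 0.75 = 30 and 40 × 0.90 = 36 participants for analysis. Approximate 95% limits for a correlation are tanh(atanh(r) ± 1.96/√(n − 3)).

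- r = 0.50, n = 30: atanh(0.50) = 0.549 and 1.96/√27 = 0.377, giving 0.17 to 0.73.
- r = 0.50, n = 36: 1.96/√33 = 0.341, giving 0.21 to 0.71.
- r = 0.70, for comparison: 0.45 to 0.85 at n = 30, and 0.48 to 0.84 at n = 36.

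The value 0.50 is illustrative, and the 95% level is assumed. These limits are for Pearson correlations at full numbers. For coping they are a best case: Spearman limits are somewhat wider, a participant contributes only if negative events are reported, and numbers may fall at phases 2 and 3.

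**The case against.** The strongest reply is that coping validity appears as an aim only in the abstract. The formal primary objective names neither coping nor validity, so the mismatch could be cured by correcting the abstract. That stands, and it is why narrowing the aim is offered as an alternative. It does not remove the point: the document currently states an aim that its listed analysis does not answer.

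A second reply is that an article condenses the full protocol. For coping this does not persuade, because the section gives the indexes, the statistic, the eligibility threshold and each pairing; a list that detailed which omits a construct named in the aim is a mismatch, not an abbreviation. For reliability the reply has more force. An article may well leave the choice of estimator to the full protocol, and reliability may be used loosely for validity, although the discussion lists the two separately. That part is therefore secondary.

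A third reply is that the two coping instruments differ. The Brief-COPE is used in its dispositional form, reworded for stroke-related stress, whereas EMA asks about the most negative event of the preceding hours. Modest correlations would therefore not be decisive. This is right, and it argues for exploratory estimates without a pass mark.

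Several stronger readings are tempting but unsupported:

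- That the whole primary analysis is confined to mood. Compliance, missing data, duration and fatigue apply to the full EMA interview, coping items included; only the validity part is confined.
- That coping is the only untested measure. Other items were also adapted or built for the study; coping is simply the one called original.
- That objective 2 depends on EMA coping. It can be met with the Brief-COPE, for which a French validation is used.
- That 14 of the 32 screens go unvalidated. This assumes one screen per sentence, which the article does not state; context and event items have no validity pairing either.

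**Conclusion.** The concern holds for coping. The abstract names three constructs for validation, and the listed validity analysis covers two. Of six pairings none involves coping, and secondary analysis (4) adds symptoms only. The consequence is clearest for objective 5, where EMA coping is used explicitly. That limits the damage, since the article describes the work on symptom dynamics as largely exploratory.

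Reliability is a lesser finding: it is claimed in two places and estimated in none of the listed analyses, but the full protocol may supply the estimator.

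The conclusion does not depend on any numerical assumption. The count of 14 pairs per phase does depend on one-to-one matching of sentences to subscales, and the precision figures depend on 30 to 36 participants contributing usable coping data.

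**What to change.** **Coping.** For each participant and phase, define the EMA coping score for each sentence as the proportion of yes answers among prompts at which a negative event was reported. Where the item wording supports one-to-one matching, report exploratory Spearman correlations with 95% confidence intervals against the corresponding Brief-COPE subscale: up to 14 per phase and 42 over three phases. Do not carry over the 0.70 benchmark, because the two instruments ask about different stressors. Report alongside each estimate the number of participants contributing and how many negative-event prompts they supplied.

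If this is not wanted, narrow the abstract's aim to the validity of anxiety and depression EMA, and say in the report of objective 5 that the EMA coping items have not been validated. Either way, bring the abstract and the Objectives section into line on what is being evaluated.

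**Reliability.** For each EMA index and phase, add either a split-half correlation (for example odd against even days) or the between-person share of variance. Otherwise remove reliability from the primary objective and from the clinical implications.

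**Cost.** Analysis time only, with no new data and no added burden for participants. The downside is more exploratory estimates, less precise than those for the mood indexes where few negative events are reported or participants are lost at follow-up.

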#### Sample Size

Forty participants will be included in the study. According to previous research using EMA for psychological assessment, an acceptance rate between 75 and 90% is expected (Johnson et al., 2009a,b). Thus, we expect data from 30 to 36 participants to perform analysis.

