## Discussion

### Anticipated Results

#### Primary Objective

A participation rate at inclusion between 75 and 90% is expected regarding previous results with EMA method (Johnson et al., 2009a,b). The completion rate of EMA questionnaires is expected to be at least of 80% for the entire group during each phase (Sibon et al., 2012). In order to have satisfying validity, correlations between EMA indexes and data collected using other methods are expected to be higher than 0.70.

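### The five-questionnaire entry rule does not secure the within- and between-day compliance it is said to represent, and 30 to 36 participants cannot separate correlations of about 0.60 to 0.80 from the 0.70 benchmark

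*Protocol article*

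**What the plan says.** The section on outcomes and statistical methods for the primary objectives describes the validity analysis: "Validity will be assessed by using Pearson correlations between EMA indexes with self-reported questionnaires’ scores and clinicians’ ratings". It lists six pairs:

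- the global index with the HADS total;
- the depression index with the BDI, the HADS depression subscale and the MADRS;
- the anxiety index with the HADS anxiety subscale and the HAM-A.

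Entry to this analysis is restricted: "Only participants with a satisfying minimum within- and between-day compliance will be included in this analysis (i.e., at least 5 EMA questionnaires filled". The same section sets the denominator for compliance within a phase: "four questionnaires per day during 7 days for each participant".

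Under Anticipated Results, Primary Objective, two expectations are given. On completion: "The completion rate of EMA questionnaires is expected to be at least of 80% for the entire group during each phase". On validity: "In order to have satisfying validity, correlations between EMA indexes and data collected using other methods are expected to be higher than 0.70".

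The Sample Size section says "Forty participants will be included in the study" and, after applying the expected acceptance rate, "Thus, we expect data from 30 to 36 participants to perform analysis".

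**The concern.** The entry rule names a property, adequate compliance both within and between days, and then defines it by a total count. A total does not control how answers are distributed. A participant can qualify with almost all answers on one day, or with a single answer on each of several days. An index meant to describe a week may then rest on very little of it, and sparse indexes are noisier and pull a correlation down. The rule also does not say whether five answers are needed in each phase or in the whole study. Under the second reading, a participant could contribute a later-phase index built on one or two answers.

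The second issue is what is then done with the correlation. The only validity criterion in the article is a value above 0.70, given without an interval or bound. The sample size comes from acceptance alone, not from the precision of a correlation. If the true correlation lies near the benchmark, whether the estimate falls above or below it is largely chance, and validity is part of the primary objective.

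**Working it through.** **The plan's own figure.** 40 × 0.75 = 30 and 40 × 0.90 = 36, which reproduces the stated 30 to 36. This allows for acceptance only. Drop-out by the later phases and the entry rule can only lower it.

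**What five answers guarantee.**
- Prompts: 4 × 7 = 28 per phase and 3 × 28 = 84 over the study. So 5/28 = 17.9% and 5/84 = 6.0%. The expected 80% is 0.80 × 28 = 22.4 per phase.
- Between days: at most four answers fit in a day, so five always touch at least two days. Four on one day and one on another qualifies.
- Within days: one answer on each of five days qualifies. Five answers can be placed in the 28 slots in C(28,5) = 98,280 ways, of which C(7,5) × 4⁵ = 21,504 (21.9%) have no day with two answers. This counts layouts; it does not predict behaviour.

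**How much this could move a correlation.** The documents give no variance components, so these are assumptions. Let the person, day and moment shares be vp, vd and vm, and let a participant give c_j answers on day j, n in total. The error variance of the person mean is vd·Σ(c_j/n)² + vm/n, and the observed r is the true r × √[vp/(vp + mean error variance)]. Take a true r of 0.80 and shares 0.4/0.2/0.4:
- 4 + 1 answers: 0.2 × (0.64 + 0.04) + 0.4/5 = 0.216.
- 80% completion spread evenly: 0.2/7 + 0.4/22.4 = 0.046.
- Nobody at the minimum: r = 0.757.
- 10% at the 4 + 1 minimum: mean error variance 0.063, r = 0.743.
- 20% at the minimum: mean error variance 0.080, r = 0.730.

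The loss is 0.014 to 0.027. Other assumed shares give:

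| Shares (person/day/moment) | 0% at minimum | 10% | 20% |
|---|---|---|---|
| 0.6/0.1/0.3 | 0.782 | 0.776 | 0.770 |
| 0.4/0.2/0.4 | 0.757 | 0.743 | 0.730 |
| 0.3/0.2/0.5 | 0.740 | 0.721 | 0.704 |

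Across the three sets the loss runs from about 0.01 to 0.04.

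**Precision against 0.70.** Fisher z: atanh(0.70) = 0.867, with SE = 1/√(n − 3), which is 0.192 at n = 30 and 0.174 at n = 36.
- Observed 0.70, n = 30: tanh(0.867 ± 1.96 × 0.192) = 0.45 to 0.85.
- Observed 0.70, n = 36: tanh(0.867 ± 1.96 × 0.174) = 0.48 to 0.84.
- Observed 0.80: 0.62 to 0.90 (n = 30) and 0.64 to 0.89 (n = 36). Both still include 0.70.
- Observed 0.60: tanh(0.693 ± 1.96 × 0.192) = 0.31 to 0.79 (n = 30). This also includes 0.70.
- A lower limit above 0.70 needs an observed r of about 0.85 (n = 30) or 0.84 (n = 36).

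The chance that the observed r exceeds 0.70 is 1 − Φ[(0.867 − atanh ρ)/SE]:

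| True correlation | n = 30 | n = 36 |
|---|---|---|
| 0.50 | 5% | 3% |
| 0.60 | 18% | 16% |
| 0.70 | 50% | 50% |
| 0.80 | 89% | 91% |

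**The case against.** Several points on the other side have force.

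- *Spread over days.* A reader might infer that the rule secures no spread over days at all. That is wrong: five is the smallest count that forces a second day when there are four prompts a day. What stands is that two of seven days is weak and that nothing is secured within days.
- *Size of the attenuation.* It is tempting to say that a true 0.80 would be seen as 0.64. Under the 0.4/0.2/0.4 shares that needs every participant to sit at 4 + 1 answers, while the article expects at least 80% completion. If completions were independent at 80%, practically nobody would fall below five. The rule matters mainly if non-response clusters in some participants.
- *Aggregation and number of correlations.* The article does not say how prompts are combined into an index. An unweighted mean is therefore an inference, and such detail may be left to the full protocol or analysis plan. Combining Table 1 with the six pairs suggests 14 concurrent correlations (4 at discharge, 4 at two months, 6 at four months), but the text does not state this count.
- *Status of 0.70.* The methods section sets no pass/fail rule, and the figure appears once, as an expectation in the Discussion. A formal point-estimate test is not supported by the text, and the absence of intervals from a condensed article is not in itself an error. Even so, the sentence ties adequate validity to that value, no other criterion is given, and an analysis plan that added intervals would not change the precision fixed by 30 to 36 participants.
- *Existing multilevel work.* Means-as-outcomes modelling is already planned, but for a secondary objective and at the level of single symptoms.

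**Conclusion.** The point holds in two limited parts.

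First, the entry rule does not deliver the property by which it is described, and its scope (phase or study) is open. This follows from the text and from counting. The consequence for the correlations is probably small: about 0.01 to 0.03 in r with 10 to 20% of participants at the minimum under one assumed set of variance shares, and up to about 0.04 under another. It would be larger with clustered non-response.

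Second, with 30 to 36 participants, correlations of roughly 0.60 to 0.80 cannot be told apart from 0.70. This rests only on the stated sample size, the Fisher z approximation and a 95% level. It does not mean that the study is uninformative about validity, since a true correlation near 0.50 would exceed 0.70 only 3 to 5% of the time. The plan should be changed, but the matter does not threaten the study as a whole.

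**What to change.** Apply the entry rule separately in each phase and state it as a minimum number of days together with a minimum number of prompts per day. At least two answered prompts on each of at least three days is one example; the exact cut-off is a matter of judgement and should be fixed before the data are seen. Keep the set with at least five questionnaires as a sensitivity analysis.

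Report every validity correlation with its 95% confidence interval, base the validity statement on that interval, and treat 0.70 as a reference value. Name one lead correlation for depression and one for anxiety, each at a stated phase. A multilevel model that weights participants by their number of prompts is an optional further sensitivity analysis.

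The cost is analysis wording only, with no added participants or visits. A few sparse responders leave the main correlation, and the validity claim becomes more cautious. The imprecision itself remains at this sample size, but it becomes visible in the conclusion.
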